### Randomization

A randomization list of 115 baseline periods (2–12 weeks, with an equal distribution between the 11 intervals) is generated using the statistical program SPS. Upon signing informed consent, the participant receives the baseline period corresponding with the next open slot on the list.

### Outcomes and measurements

#### Primary outcome

The primary outcome is a set of patient reported outcome measures (PROMs) containing questions directly or indirectly related to sensory processing difficulties, which will be filled in by caretakers. We chose this outcome over more conventional outcome measures for three reasons. 1) it allows for more personalized method of outcome measuring, 2) the PROMs are selected based on the symptoms not captured by conventional outcome scales (see background), 3) A prerequisite for the primary outcome of a SCED is the frequent and repeated measurement of the target behavior in every phase to address the variability in that behavior during the baseline and the intervention phase. The selected PROM-set asks the respondent to reflect upon the last 7 days, whereas conventional questionnaires often ask for reflection upon a longer time scale, making them less suitable for a SCED design.

The effects on PROMs will be compared to main conventional endpoints used in the original trials (social responsiveness scale, second edition (SRS-2) [17], repetitive behavior scale revised (RBS-r) [18], aberrant behavior scale (ABC) [19] and sensory profile – Dutch version (SP-NL) [20]) as well as accompanying measurements of EEG and neurocognition to further establish effects on brain activity and functioning and to validate predictive markers of treatment response. Individual results will be aggregated to evaluate bumetanide efficacy on a group level.

#### Secondary outcomes

The secondary outcome measures are divided over three domains: the behavioral, the functional and the translational domain (see Table 4).

**Table 4 Tab4:** Outcome measures

Domain	Outcome measure
**Primary outcome measures**	
**Behavioral domain**	
**Anxiety**	PROMIS Anxiety (v2.0) PROMIS Psychological stress experiences (v1.0)
**Mood problems**	PROMIS Depressive symptoms (v2.0) PROMIS Life satisfaction (v1.0)
**Sleep problems**	PROMIS Sleep-related impairment (v1.0) PROMIS Sleep disturbance (v1.0)
**Fatigue**	PROMIS Fatigue (v2.0)
**Physical complaints**	PROMIS Physical stress experiences (v1.0)
**Daily functioning and participation**	PROMIS Cognitive function (v.1.1), VABS
**Problems in social interaction and communication**	PROMIS Peer relationships (v2.0)
**Secondary outcome measures**	
**Behavioral domain**	
**Social communication and interaction**	SRS-2 (subscales social awareness, social cognition, social communication, social motivation)
**Restricted, repetitive patterns of behavior**	SRS-2 (subscale mannerisms) RBS-r
**Sensory stimulation tolerance**	SP-NL
**Sensitivity to sensory stimuli**	SP-NL
**Aberrant behavior**	ABC
**Functional domain**	
**Cognitive**	Emma-toolbox
**Neurophysiological**	rsEEG
**Translational domain**	
**Genetic**	Whole exome sequencing
**Cellular**	Assays on iPSC-derived neuronal models

*ABC* Aberrant behavior scale, *PROMIS* patient reported outcome measurement information system, *RBS-r* repetitive behavior scale revised, *rsEEG* resting state electro-encephalogram, *SP-NL* sensory profile, Dutch version, *SRS-2* social responsiveness scale, second edition, *VABS* Vineland scale of adaptive behavior

##### Behavioral domain

The behavioral domain focuses on clinical outcomes and constitutes of four questionnaires to evaluate core symptomatology. The scales used are consistent with those used in the previous trials: The SRS-2, RBS-r, ABC and SP-NL.

In addition, these questionnaires will be used to validate how well the PROM set captures classically defined core symptomatology.

##### Functional domain

The functional domain contains neurocognitive and neurophysiological measures. We will use the Emma Tool box, an in-house designed battery of computerized tests, to measure neurocognitive functions in children. Measures will be obtained at 3 time points (baseline and after three and 6 months of treatment). Individual change in domain scores will be analyzed.

We will perform resting state electroencephalography (EEG) to assess neurophysiological functioning. EEG will be recorded by using the 128 channels Magstim/EGI system. EEG data will be processed offline using the Neurophysiological biomarker toolbox (http://www.nbtwiki.net/). Similar to our previous trials we selected five biomarker algorithms that have proven sensitive to the ratio of excitation and inhibition in computational models of neuronal networks generating alpha-band oscillations to quantify EEG. These biomarkers include: Relative and absolute power, central frequency, detrended fluctuation analysis and excitation/inhibition ratio. EEGs will be obtained at baseline, Tmax (1,5 h after first dose) and shall be repeated on a monthly basis.

##### Translational domain

The translational domain focusses on methods for future translation of (emerging) disease mechanisms and the development of more personalized therapies.

One entry point for personalized therapies are studies in animal models with causal genetic variants for NDDs. Hence, we will perform genetic testing via whole exome sequencing.

In addition, induced pluripotent stem-cell (iPSC) based model systems provide the opportunity to examine disease mechanisms in patient-own neurons and provide the opportunity to test personalized treatment options. Accordingly, we will perform assays with iPSC derived neuronal models.

#### Safety procedures

Safety will be assessed by the research team under supervision of a child psychiatrist and if necessary, a pediatric nephrologist. The assessment includes checks for the use of other medications, side effects and adverse events. In addition, physical examinations and blood and urine laboratory tests will be performed. See appendix 1 for a schematic overview of the examinations.

Oral potassium supplementation at a dose of 0.25 mmol/kg twice daily will be prescribed via custom pharmacy to all participants in order to avoid hypokalemia. Additionally, adjustments in the dosage of bumetanide are allowed to manage hypokalemia and/or side effects.

### Statistics

#### Power calculations

Without using any kind of data simulation, we estimate that 50% of the patients that were enrolled in the three previous bumetanide randomized controlled trials (RCTs) will be eligible and motivated to be enrolled in the present study (i.e. 75 patients). To estimate sample size requirements and type I and II error magnitudes of a statistical test in a SCED design, the outcome measure that is assessed on the most frequent basis should be used, in our case the PROMs. Since this measure has not been included in the previous RCTs conducted in our patient cohort, we cannot rely on effect size estimates for this particular outcome. As such, due to availability we based the power computations on outcome measures used in the BAMBI study. Specifically, we established the minimal sample size required to detect a significant effect on the secondary BAMBI outcome, improvement on repetitive behavior scale, on which previously, a significant effect was observed.

For this purpose we used an online tool suitable for multiple baseline single case designs [21]. The tool tests a statistically significant effect using a non-parametric, randomization test (see *Data Analysis*) and the following inputs: effect size to be estimated, number of permutations, number of patients, number of outcome measurements.

In a randomization test, an effect estimate is obtained by drawing a large number of samples from a “randomization distribution”. To overcome the computational difficulties arising from drawing all the possible samples, using Monte Carlo sampling we approximate as accurately as possible the result we would get when drawing all samples. To ensure a compromise between accuracy and computational feasibility, our power simulation uses repeated draws, namely 5 Monte Carlo chains, each drawing 100 samples.

We tested whether, given the current experimental setup, we are able to detect an effect comparable in size to the one obtained in the BAMBI study. For RBS-r, the outcome variable previously shown to be significantly impacted, the effect size of the treatment was estimated to be *d =* 0.373 (80% C.I. 0.225–0.529), using Cohen’s *d* for dependent samples. The simulations showed that an effect size *d =* 0.4 can be detected with a relatively high power (0.71 when *N =* 40 and 0.73 when *N =* 50), in the absence of autocorrelation. In practice, measurements which are close in time are related, thus outcome scores at one time point can predict scores at another time point (autocorrelation or serial dependence). With larger sample sizes (*N =* 60), the power to detect the same effect remains fairly high (0.69) even in the presence of low-medium (*r =* 0.3) autocorrelation.

Thus, *N =* 40 is an acceptable minimum sample size to be able to detect the BAMBI effect in a no-autocorrelation scenario and *N =* 60, a minimum sample size in the presence of low-to-medium autocorrelation. As we intend to enroll a minimum of 75 patients from previous cohorts and a minimum of 40 patients in the new cohort, we expect to have sufficient power to detect a comparable treatment effect.

#### Data analysis

For the data analysis visual inspection of the data and statistical inference using (interrupted) time series analysis and randomization tests will be performed.

##### Visual inspection using 2SD-band method

First, the PROMs will be plotted as its own time-series for visual inspection using the 2-SD band method, as described in Hoogeboom et al. [22]. The 2-SD band will be calculated from the baseline data and graphed from the baseline through the intervention and post-intervention phase. If two or more successive data points in the intervention or post-intervention phase fall outside the 2 SDs bandwidth, the result will be considered significant on an individual basis. As autocorrelation can bias the visual inspection, we will check our data in each phase for serial dependence using the lag-1 method. If data are found to be significantly correlated, we will transform the data using a moving-average transformation.

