**Method/design:**

Participants of the three previous cohorts and a new cohort will be subjected to 6 months bumetanide treatment using multiple baseline Single Case Experimental Designs. The primary outcome is the change, relative to baseline, in a set of patient reported outcome measures focused on direct and indirect effects of sensory processing difficulties. Secondary outcome measures include the conventional questionnaires ‘social responsiveness scale’, ‘repetitive behavior scale’, ‘sensory profile’ and ‘aberrant behavior scale’. Resting-state EEG measurements will be performed at several time-points including at Tmax after the first administration. Assessment of cognitive endpoints will be conducted using the novel Emma Tool box, an in-house designed battery of computerized tests to measure neurocognitive functions in children.

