### Design

We will use multiple baseline SCEDs (MBD) in which the intervention (bumetanide) is introduced sequentially to different patients with a baseline period ranging from 2 to 12 weeks. The rationale for this multiple baseline is that apart from clinical and response heterogeneity across individuals also symptoms per patient vary over time. In an MBD the variation in the baseline period (A phase) is compared to the variation during the intervention (B phase) on an individual level (i.e. the participant serves as his/her own control). Evidence of such an AB designs is based on demonstrating that the change in behavior only occurs during intervention.

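### The fixed 2-SD band, estimated from each child's own short baseline, flags about 30% of series with no drug effect (assuming weekly scores), so its label of individual significance is not supported

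*Protocol article*

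**What the plan says.** Under the heading on visual inspection, each PROM is plotted as a time series for the child. "The 2-SD band will be calculated from the baseline data" and is then carried forward through the later phases. The decision rule is: "If two or more successive data points in the intervention or post-intervention phase fall outside the 2 SDs bandwidth", then "the result will be considered significant on an individual basis". The section states no direction, no minimum number of baseline scores and no error rate. It does plan a lag-1 check for serial dependence, with a moving-average transformation if dependence is found.

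The Design section introduces treatment "with a baseline period ranging from 2 to 12 weeks". The Randomization section spreads the lengths evenly: "A randomization list of 115 baseline periods (2–12 weeks, with an equal distribution between the 11 intervals". The abstract gives the treatment phase: "Participants of the three previous cohorts and a new cohort will be subjected to 6 months bumetanide treatment". How often the PROMs are completed is not stated. The nearest indication is under Primary outcome: "The selected PROM-set asks the respondent to reflect upon the last 7 days".

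**The concern.** A band of mean plus or minus 2 SD has its familiar coverage only when the mean and SD are known, or estimated from many observations. Here both come from one child's baseline, which may hold very few scores, and the factor is not widened to allow for that. The rule then has a whole treatment phase in which to find one pair of successive points outside the band, and as worded it accepts excursions in either direction, including deterioration.

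Individual effect measurement is a stated reason for choosing this design. If many series are flagged with no drug effect, and the rate varies with the baseline length a child happens to draw, a flag cannot be read as evidence at any known error level.

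**Working it through.** The article gives no error rate for this rule, so there is no figure of its own to reproduce. The power figures in Power calculations concern the group randomization test.

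**Inputs from the article.** Baseline of 2 to 12 weeks, 11 lengths equally represented; 6 months of treatment, about 26 weeks; two or more successive points outside the band; autocorrelation 0.3, the low-to-medium value in Power calculations.

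**Assumptions.** Weekly scores (suggested by the 7-day recall), so k = 2 to 12 baseline scores and 26 treatment scores; normal data; no trend; no drug effect; sample SD with divisor k − 1.

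**Step 1: known mean and SD.** One score falls outside with probability p = 2(1 − Φ(2)) = 0.0455. Let a be the probability of no flag so far with the last score inside, and b the same with the last score outside. Start at a = 1, b = 0 and update a → (a + b)(1 − p), b → a·p. After 26 steps the flag probability is 1 − a − b = 0.0485, about 5%.

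**Step 2: one score against an estimated band.** A new score minus the baseline mean has variance σ²(1 + 1/k), and the SD has k − 1 degrees of freedom. The chance of falling outside is therefore P(|t with k − 1 df| > 2/√(1 + 1/k)):
- k = 2: P(|t₁| > 1.633) = 0.350
- k = 5: P(|t₄| > 1.826) = 0.142
- k = 12: P(|t₁₁| > 1.922) = 0.081

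Against 0.0455 in step 1, these show where the excess arises. All scores of a child share the same misestimated band, so the flag rate over the series has to be simulated.

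**Step 3: flag rate over 26 treatment scores, no effect** (simulation, at least 40,000 series per baseline length).

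| Condition | k = 2 | k = 5 | k = 12 | Mean over the 11 lengths |
|---|---|---|---|---|
| Either direction, r = 0 | 58% | 33% | 17% | 30% |
| Either direction, r = 0.3 | 70% | 49% | 30% | 44% |
| Improvement only, r = 0 | 36% | 15–16% | 6.5% | 15% |
| Improvement only, r = 0.3 | 47% | 27–28% | 16% | 25% |

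The r = 0.3 rows are before the moving-average step.

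**Step 4: other scoring frequencies** (either direction, r = 0).
- Twice weekly, 52 treatment scores: 48%, 27% and 19% with 4, 12 and 24 baseline scores.
- Fortnightly, 13 treatment scores: 50% down to 19% with 2 to 6 baseline scores. A 2-week baseline could then give a single score and no SD.

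**Step 5: the moving-average step.** No window is stated. With an assumed two-point window on independent data, the null flag rate rises to 81%, 66% and 44% for k = 3, 5 and 12. Averaging neighbours induces serial correlation and shrinks the baseline SD.

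**Step 6: response to a true shift** (either direction, r = 0, mean over the 11 lengths).

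| Shift in within-child SDs | 0 | 0.4 | 1 | 2 |
|---|---|---|---|---|
| Flagged | 30% | 34.5% | 55% | 89% |

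**Step 7: a calibrated limit.** Take the 95th percentile, under no effect, of the largest value over treatment of the smaller of two successive standardised scores in the improving direction. Without autocorrelation this gives factors of about 16, 3.0 and 2.1 for k = 2, 5 and 12.

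**The case against.** The strongest reply is that this is a first graphical step. The Data analysis section separates visual inspection from inference by interrupted time series and randomization tests, and the group effect comes from aggregated single-case estimates, not from these flags. The method is taken from a cited source, and a condensed article may leave a minimum number of scores or a direction to the full protocol. This stands as a limit on scope: group efficacy is untouched. It does not rescue the rule, because the article itself attaches a verdict of individual significance to it, and neither the citation nor the other analyses withdraw or calibrate that verdict.

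Four stronger readings are tempting and should not be drawn.
- That individual results are mostly noise. This depends on the share of true responders and on their within-child effect, neither of which is given. With 30% to 70% true responders and shifts of 0.4 to 2 SD, the false share of flags runs from 67% down to 13%. The other individual analyses also remain.
- That the flag hardly depends on the drug. Discrimination is poor at 0.4 SD, but shifts of 1 and 2 SD are flagged in 55% and 89%. The article's d of about 0.4 is a group figure on the RBS-r, not a within-child PROM shift.
- That the rule decides who is a responder. The MCID section treats that separately with an anchor-based method.
- That one flag among the ten PROMIS scales makes a child positive. No such rule is stated.

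A reader may also see a contradiction between counting post-intervention points and the design logic that "the change in behavior only occurs during intervention". The section on interrupted time series uses the same term for measurements compared with the baseline prediction, so this may be loose wording. It plays no part in the figures.

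**Conclusion.** The rule is wrong as written for the label it carries. Under weekly scoring, 26 treatment scores, normality and independence, about 30% of no-effect series are flagged against about 5% for a band with known mean and SD. The excess comes from keeping the factor at 2 with few baseline scores. The 58% applies only to the 2-week baseline, about 1 child in 11. The null rate ranges from 17% to 58% with the randomly drawn baseline length, a wider spread than the gain of about 5 percentage points from a true 0.4 SD shift.

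Weekly scoring is an assumption and the exact figures move with it. The fault itself persists under the other frequencies and the autocorrelation tried, and on average also when only improvement counts, although improvement-only with independent scores comes down to 6.5% at 12 baseline scores.

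**What to change.** Replace the fixed factor 2 by a limit calibrated by simulation to 5% for each child's number of baseline scores and for the autocorrelation pooled over participants. The factors in step 7 show the size of the change without autocorrelation. Alternatively, use a within-child SD pooled over participants, with the limit calibrated in the same way, since the child's baseline mean is still estimated from few scores. In either case:
- count only successive points on the same side, in the improving direction;
- make no individual call from a child's own SD with fewer than 5 baseline scores.

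If the sponsor prefers to keep the plain 2-SD band, describe it as a descriptive display and drop the word significant.

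The cost is one simulation and some rewording; visits and treatment do not change. The downside is fewer individual calls. Under weekly scoring, baselines of 2, 3 and 4 weeks fall below five scores, which is 3 of 11 lengths, or about 31 of 115 children (3/11 × 115 = 31.4). They would get no call unless the pooled SD is used.

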##### Parametric methods: (interrupted) time series

Single subject measurements are graphed over time in a series based on which we can predict measurements at future time points for that subject.

Due to repeated measurements, the series may exhibit patterns such as autocorrelation, seasonality and trends not explained by the intervention (non-stationarity). Failing to account for said patterns can lead to erroneous effect predictions. Based on visual inspection of the series and residuals, special regression models “*ARIMA”* (*AR* auto-regressive, *I* integrated, *MA* moving-average) can be tailored to account for said patterns and get more accurate predictions. To obtain group effects, the single-case effect predictions will be aggregated using meta-analysis.

Given our study design we are interested in comparing the (predicted) outcome evolution based on the baseline measurements, to the (observed) evolution based on post- intervention measurements. To that aim we use interrupted time series analysis (ITSA), an extension of classical time series analysis [23].

##### Non-parametric methods: randomization tests

If the SCED involves a small number of participants, parametric assumptions of data normality and homogeneity of variance might not be met, in which case, tests which do not make parametric assumptions might be more suitable, i.e. Koehler and Levin’s randomization test [24].

The null hypothesis of the randomization test is that, for all possible permutations, the mean difference between baseline and intervention is the same.

##### Selection bias

There is a likelihood of (patient-induced) selection bias, as it is more likely that previous participants from the responder groups will participate in this post trial access study. Accordingly, there will probably be a larger group of responders than non- responders.

We propose two methods to address this: controlling for covariates associated with selection (modelling-based) and inverse probability weighting. In the first approach, we will include a covariate describing previous responder status and check for significance. The second approach involves computing the probability of selection for each responder category and assigning a weight to each subgroup inverse to the selection probability.

#### Minimal clinically important difference (MCID)

Another aspect we wish to address is what constitutes a (non)responder. To determine the MCID for our target outcome scales, we intend to use comparisons of care-taker assessments in parent-to-parent conversations (anchor-based method).

#### Development of new predictors

The newly developed prediction algorithm based on EEG and clinical features will be evaluated and further developed [16]. Analyses will be performed using both regression analyses and supervised machine learning.

## Discussion

In conclusion, the BUDDI post trial access study will offer the opportunity to replicate individual and stratified group level effects of bumetanide, to improve clinical endpoint selection and to validate an EEG based treatment prediction algorithm. Forthcoming findings may enhance the applicability of bumetanide in heterogeneous NDD populations.

